***Mortality outcomes assessed at ICU discharge, 28 days, hospital discharge and 90 days***
11.***Composite outcome of lower-extremity DVT, PE and 28-day mortality***
**to** address the competing risk of VTE and mortality [12, 13]12.Serial respiratory, cardiovascular Sequential Organ Failure Assessment (SOFA) scores13.Serial daily fluid intake, output and balance and vasopressor doses

### Statistical analysis

Categorical variables will be reported as numbers and frequencies, and will be compared using the chi-square test. Continuous variables will be reported as mean and standard deviation or median and interquartile ranges (IQR, Q1–Q3). Continuous variables will be tested using the Student’s *t* test or the Wilcoxon-Mann-Whitney test, as judged appropriate by normality testing. For serial measurements, we will test the change over time and the difference between the two groups over time using a repeated-measures analysis of variance, with no imputation for missing values. For serial measurements, we will use the Bonferroni correction to account for multiple comparisons. Associations will be reported as risk ratios (RR) or hazard ratios (HR) with 95% CIs. Unless otherwise specified, tests will be two-sided and at the 5% significance level. All statistical analyses will be conducted using the SAS software version 9.1.3 or higher (SAS Institute, Cary, NC, USA).

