## Methods/design

### Study design

The PREVENT trial will enroll 2000 critically ill patients from 16 hospitals in 4 countries. The study has been approved by the Institutional Review Boards (IRBs) of the participating sites. The trial is registered at ClinicalTrials.gov: (NCT02040103) and Current Controlled Trials (ISRCTN44653506). The study is sponsored by King Abdulaziz City for Science and Technology (Grant number AT 65-34) and King Abdullah International Medical Research Center (Protocol number RC12/045/R), Riyadh, Saudi Arabia. The sponsors have no role in the study design, management or analysis.

All patients will be screened for eligibility within 48 h of ICU admission. Medical-surgical-trauma ICU patients, using accepted age cut-offs in participating adult ICUs (e.g. ≥ 14, 16 or 18 years), who weigh ≥ 45 kg, are expected to stay in ICU for ≥ 72 h and are eligible for pharmacologic thromboprophylaxis with either UFH and LMWH will be enrolled (Fig. 1). Exclusion criteria have been detailed in the protocol manuscript [5]. To enhance the generalizability of our findings, we permit the use of a broad array of IPC devices from various manufacturers intended for DVT prophylaxis. These devices include sequential devices (multi-chamber cuffs) and non-sequential devices (single-chamber cuff); the type of device will be recorded. IPC will be applied continuously for at least 18 h per day. The study intervention will continue for the duration of the ICU stay or up to 28 days after randomization; after which IPC use will be at the discretion of treating team. All enrolled patients will have a bilateral lower-extremity ultrasonography performed by a certified technologist at baseline (within 48 h of enrollment) and twice weekly thereafter until the diagnosis of a lower-extremity DVT or PE, ICU discharge, death, full mobility or 28 days (Fig. 2).

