### Primary outcome

The primary outcome is incident proximal lower-extremity DVT detected after the third calendar day of enrollment during the intervention period (defined as the number of calendar days from enrollment until the end of the intervention period; that is, diagnosis of lower-extremity DVT, PE, ICU discharge, death, full mobility or 28 days). The primary outcome tests the primary hypothesis that IPC reduces incident proximal lower-extremity DVT (Additional file 1: Table S3).

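### Repeated-measures ANOVA without imputation, in its classical form, would limit the serial ICU outcomes to patients observed on every analysed day; the plan should name an all-available-data mixed model

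*Protocol article*

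**What the plan says.** The Statistical analysis section of the protocol article sets one rule for all serial measurements. The aim is stated as follows: "we will test the change over time and the difference between the two groups over time". The method and the missing-data rule for that aim are given as "using a repeated-measures analysis of variance, with no imputation for missing values". It adds: "For serial measurements, we will use the Bonferroni correction to account for multiple comparisons". On software it says only: "All statistical analyses will be conducted using the SAS software version 9.1.3 or higher". It names no procedure and no within-patient covariance.

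The outcomes concerned are items 12 and 13 under Secondary outcomes: "Serial respiratory, cardiovascular Sequential Organ Failure Assessment (SOFA) scores" and "Serial daily fluid intake, output and balance and vasopressor doses". The daily mobility level described under Mobility may also fall under this rule.

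Two other sections bear on the point. Under Primary outcome, the intervention period ends at "diagnosis of lower-extremity DVT, PE, ICU discharge, death, full mobility or 28 days", so its length differs from patient to patient. Under Analysis of secondary outcomes, the analysis set is the intention-to-treat cohort.

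**The concern.** Classical repeated-measures ANOVA needs a full row of values for each patient. If one day is missing and nothing is imputed, the patient leaves the analysis. For daily ICU measures, an incomplete series is the expected pattern: death ends it, and leaving the ICU very probably does. The patients retained would be those still observed on the last analysed day.

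That set is defined by survival and length of stay, both of which follow randomisation. It departs from the intention-to-treat cohort and describes a different population. If IPC affected stay or survival, the comparison between arms could be biased. Even without bias, the observed days of everyone who left early would go unused.

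**Working it through.** **Inputs.** The article gives no figure for the serial outcomes, so there is none to reproduce. The planned enrolment of 2000 (Study design) serves only as a denominator. The maximum follow-up comes from the same section: "The study intervention will continue for the duration of the ICU stay or up to 28 days after randomization". The distribution of ICU stay and the number of days analysed are not given, so the shares below rest on assumptions.

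**Share with a complete series.** Assume a constant daily exit rate (discharge or death combined) and a median stay of m days, with enrolment as day 1. The share still observed on day d is

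S(d) = 0.5^((d − 1)/m).

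For example, with m = 5 and d = 7, S = 0.5^(6/5) = 0.435; with m = 14 and d = 7, S = 0.5^(6/14) = 0.743.

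| Last analysed day | m = 5 | m = 7 | m = 10 | m = 14 | Patients of 2000 (m = 5 to m = 14) |
|---|---|---|---|---|---|
| 3 | 75.8% | 82.0% | 87.1% | 90.6% | 1516 to 1811 |
| 7 | 43.5% | 55.2% | 66.0% | 74.3% | 871 to 1486 |
| 14 | 16.5% | 27.6% | 40.6% | 52.5% | 330 to 1051 |
| 28 | 2.4% | 6.9% | 15.4% | 26.3% | 47 to 525 |

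**A gentler exit pattern.** The trial enrols patients expected to stay at least 72 h, so early exits may be rarer than a constant rate implies. Suppose that exits start only at day 3 and that the mean further stay is 8 to 12 days. The complete share is then exp(−(d − 3)/mean):
- Day 7: exp(−4/8) = 0.61 to exp(−4/12) = 0.72.
- Day 14: exp(−11/8) = 0.25 to exp(−11/12) = 0.40.

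Both ranges lie inside those in the table.

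**Patients lost versus data lost.** One illustrative simulation used assumed inputs: 2000 patients, 14 days, exit dependent on the score, and a true arm-by-day slope of −0.03.
- Complete series: 986 of 2000 patients (49.3%). A mixed model, also without imputation, used all 2000.
- Observed patient-days: 73.0% of 2000 × 14 = 28,000, or about 20,450. Complete-series patients supplied 986 × 14 = 13,804, and 13,804/20,450 = 67.5% of the data that existed.
- Mean day-1 score: 3.11 in the complete-series subset against 2.99 overall (SD 1.42), a small shift in population.
- Estimated arm-by-day slope: −0.0333 (SE 0.0038) from all available data and −0.0320 (SE 0.0042) from complete series only. The standard error was about 11% larger (0.00418/0.00377 = 1.11), with no evident bias. Both estimates came from the same random-intercept model, so the contrast shows the effect of the patient set and not of ANOVA as such.

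**The case against.** A reader might infer that the plan keeps only long-stay survivors and throws away most of the data. The document does not support that.

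- It never says that incomplete series are dropped. No imputation does not mean complete cases only: the mixed model recommended below imputes nothing either. In SAS, a repeated-measures analysis of variance can be fitted by likelihood on all available days, and the team plans mixed models for the primary outcome.
- Exclusion of those who died or left the ICU applies only up to the last analysed day, which the article does not give. It may be set in the definitions table of Additional file 1, which is not shown, so its absence here is not a fault.
- Days after death never existed and cannot be discarded. In the simulation, complete-series patients held about two thirds of the observed data.
- Bias between arms requires IPC to affect stay or survival, and nothing in the article suggests that it does.
- A mixed model does not remove truncation by death or discharge.

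All of this stands, and it limits the point to how the analysis is specified. It does not dispose of it. The article presents itself as the statistical analysis plan, and it states both a method and a missing-data rule. Where the authors want a mixed model for the primary outcome they say so; here they do not. This favours the classical reading without proving it. Two analysts could follow the same sentence and analyse clearly different sets of patients.

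Classical ANOVA also assumes sphericity. That is secondary, because the standard corrections are not ruled out.

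**Conclusion.** The point holds as a cheap improvement to secondary analyses. As worded, the plan permits a classical repeated-measures ANOVA, and that form without imputation would select patients on post-randomisation stay and survival and depart from the stated intention-to-treat cohort.

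Under an assumed median stay of 5 to 14 days and constant exit, a 7-day window would exclude about 26% to 57% of patients (100 − 74.3 to 100 − 43.5), and a 14-day window about 48% to 84% (100 − 52.5 to 100 − 16.5). A 3-day window would exclude about 9% to 24%. No single figure can be fixed without the window and the stay distribution. Bias in the arm comparison is possible but not shown; loss of precision and a changed population are the surer consequences. Items 12 and 13, and possibly daily mobility, are affected. The primary outcome is not.

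**What to change.** Replace the repeated-measures ANOVA sentence with a likelihood-based linear mixed model for repeated measures:
- **Data:** all available observations in the intention-to-treat cohort.
- **Terms:** arm, day, arm-by-day interaction, baseline value and heparin stratum, with centre as a random effect.
- **Covariance:** a stated within-patient structure, such as unstructured or first-order autoregressive.
- **Multiplicity:** keep the Bonferroni correction.
- **Reporting:** the number of patients still observed, by day and arm.

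Add a sentence that death and ICU discharge truncate the series. The model relies on missingness being explained by the observed values, and it implicitly carries trajectories past the point at which patients leave, so the results need cautious reading.

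The cost is a change of wording and slightly more analysis work, with a standard procedure in the stated software. If an all-available-data fit was already intended, one sentence saying so resolves the main point.

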#### Analysis of primary outcome

The primary outcome will be compared in the intention-to-treat and per-protocol cohorts (effectiveness analysis) using chi-square test. Results will be reported as RR with 95% CI (Additional file 1: Table S5). Because some centers may have few events, we will use a generalized linear mixed-model (GLMM) used to estimate adjusted RR after incorporating center/site as random effect [14]. If there is significant difference, we will report relative risk reduction (RRR), absolute risk reduction (ARR) or increase, and number needed to treat (or harm) with 95% CIs. The unadjusted Cox proportional hazard model will also be used to test the null hypothesis and will be used as a secondary analysis tool. We define the hazard function at time *t* as the instantaneous probability of a DVT at time *t* given the patient was free of DVT up to that time. Incident DVT cases will be considered as events. Specifically, we will censor patients who are free of DVT by the end of the 28-day follow-up period, those who die before day 28, and those lost to follow-up (dropouts and lost to follow-up before day 28). We will report hazard ratio (HR) with 95% CI. Kaplan-Meier curves will be generated for the alternative treatment groups and a log-rank test will be used to compare distributions. Although imbalances in baseline characteristics are unlikely with the large sample size, we will conduct an adjusted Cox proportional hazard model with center/site as random effect to adjust for the following factors (defined a priori): enrollment center and type of heparin used (unfractionated vs. low-molecular-weight), in addition to the following variables that are strongly believed to have significant impact on DVT incidence, source of admission to ICU being the ward (compared to the emergency department, operating room and others), trauma, femoral line, dialysis and heart failure.

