### Co-interventions

#### Pharmacologic thromboprophylaxis

We will compare the two study groups for the types of pharmacologic thromboprophylaxis (UFH, LMWH) at the time of enrollment. Because pharmacologic thromboprophylaxis type may be changed by the treating teams, we will report the percentage of patients who received each type of pharmacologic thromboprophylaxis (UFH, LMWH) at any time during the intervention period and for > 50% of the study period.

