#### Subgroup analyses

The primary outcome will be compared in the intention-to-treat cohort only, in the following a-priori-defined subgroups using a chi-square test (Additional file 1: Table S5). Results will be reported using RR and 95% CI and the multivariable logistic regression will be used to report the results of tests of interactions for these subgroups:UFH and LMWH. Randomization is stratified according to the type of heparin as it may modify the protective effect of IPC on DVT, especially in trauma patients for whom LMWH may be more effective than UFHFemoral CVC at baseline and no femoral CVC at baseline. IPC may have preferential effect in patients with femoral CVC by reducing venous blood stasis. In addition, patients with femoral CVC may have higher baseline rate of DVT, and therefore IPC effect may varyTrauma, postoperative and medical admission diagnoses. IPC may have differential effects on these groups as they have different baseline risksHeart failure and no heart failure (NYHA classification grades III and IV). IPC may have differential effects on these groups as they have different baseline DVT risksEjection fraction of < 40% or ≥ 40%. This cutoff has been used in several clinical trials to define heart failure with preserved ejection fraction [15–17]. IPC may have differential effects on these groups as they have different baseline DVT risksBMI < 30 and BMI ≥ 30. Given that obesity is a risk factor for DVT, IPC may have differential effects according to BMIVasopressors versus no vasopressors. Patients on vasopressors are at increased risk for DVT; therefore, IPC may have differential effects according to vasopressor therapy [18]Country: there are differences in patient populations and clinical practices that may influence the baseline DVT risk, including mobility and duration of stay in the ICU. Therefore, IPC may have differential effects according to the countryAbove-knee sleeves compared to control and below-knee sleeves compared to controlSequential devices compared to control and non-sequential devices compared to control

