#### Sensitivity analyses

In a sensitivity analysis, we will consider all lower-extremity DVT and PE events as incident. In another sensitivity analysis, we will consider post-enrollment lower-extremity DVT and PE events if they occur on calendar day 2 or later post enrollment [13]. Because mortality can be a competing outcome with VTE, we plan a sensitivity analysis that is restricted to patients who survive and in the ICU for at least 14 days. Because baseline ultrasonography can be missing, some patients may have a positive non-baseline ultrasonography without a baseline ultrasonography examination, making it difficult to determine whether DVT was a prevelent or an incident event. In these patients, we will have a sensitivity analysis assuming that the missing baseline ultrasonography was negative for DVT and another analysis assuming that the exam was positive. We will examine dose-effect relationship by assessing the relationship of the IPC duration and incident proximal lower-extremity DVT (Table 1 and Additional file 2: SPIRIT 2013 Checklist).

**Table 1 Tab1:** Summary of analysis plan

Variables	Intention-to-treat cohort	Per Protocol cohort
Baseline characteristics	No statistical comparisons will be performed	None
Intervention and co-interventions	Chi-square, Fisher’s exact test, Mann-Whitney *U* test, *t* test as applicable	None
Primary outcome	1. Primary analysis: chi-square. Report relative risk. Generalized linear mixed model (GLMM) incorporating center/site as random effect. Report as adjusted relative risk. If a significant difference detected: relative risk reduction, absolute risk reduction and number needed to treat (or harm) will be reported 2. Secondary analyses: unadjusted Cox proportional analysis, Kaplan-Meier (KM) curves, adjusted Cox proportional analysis	1. Primary analysis: chi-square and relative risk. Generalized linear mixed model (GLMM) incorporating center/site as random effect. Report as adjusted relative risk. If a significant difference detected: relative risk reduction, absolute risk reduction and number needed to treat (or harm) will be reported. 2. Secondary analyses: unadjusted Cox proportional analysis, KM curves, adjusted Cox proportional analysis
Secondary outcomes	Chi-square. Report relative risk	None
Subgroup analyses	Chi-square. Report relative risk	None

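### The primary test omits the heparin stratum used in randomization, no single test is named as decisive at 0.048, and the absolute risk reduction is promised only after a significant result

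*Protocol article*

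**What the plan says.** - **Randomization.** Under Subgroup analyses: "Randomization is stratified according to the type of heparin as it may modify the protective effect of IPC on DVT". The article names no other stratification factor.
- **Primary comparison.** Under Analysis of primary outcome: "The primary outcome will be compared in the intention-to-treat and per-protocol cohorts (effectiveness analysis) using chi-square test". The same section adds a mixed model "used to estimate adjusted RR after incorporating center/site as random effect". Neither has a heparin term.
- **Where heparin type appears.** It is a covariate in the adjusted Cox model, which Table 1 classes as secondary, and the first pre-specified subgroup, with an interaction test by logistic regression.
- **Labels.** Table 1, intention-to-treat column: "Primary analysis: chi-square. Report relative risk. Generalized linear mixed model (GLMM) incorporating center/site as random effect". Both stand under item 1. The Cox and Kaplan-Meier analyses stand under item 2, as secondary.
- **Absolute effect.** "If there is significant difference, we will report relative risk reduction (RRR), absolute risk reduction (ARR) or increase". Table 1 repeats the condition. The Abstract sizes the trial on a fall from 7% to 4%.
- **Threshold.** Interim analyses sets the final p value at 0.048 and makes the primary outcome analysis the interim statistic, without naming the test.
- **Heparin over time.** Under Pharmacologic thromboprophylaxis: "pharmacologic thromboprophylaxis type may be changed by the treating teams". Type is therefore summarized at enrollment, at any time, and for more than half of the study period.

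**The concern.** Three parts of the primary analysis are fixed less well than they could be.

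1. Stratified randomization balances the arms on heparin type. A test that ignores the stratum counts variation between strata as noise. Its standard error is then a little too large, so it is somewhat conservative and gives up some power.
2. Two methods share the primary label. If one p value falls below 0.048 and the other above it, the plan does not say whether the trial is positive, or whether the absolute reduction and number needed to treat are to be reported. The stopping rule inherits the gap.
3. After a null result the plan does not promise the interval on the scale on which the trial was designed. That interval shows whether a 3-point reduction can be excluded.

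A smaller point goes with these. The adjusted Cox model lists heparin type, femoral line and dialysis without a time point, and all three can change after randomization.

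**Working it through.** **1. The plan's own figure.** Inputs from the Abstract and Study design: 7% against 4%, 80% power, 2000 patients, two-sided. Equal allocation is assumed, because the article gives no ratio. Mean rate 0.055, difference d = 0.03.

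n per arm = [z(α/2)·√(2·0.055·0.945) + 0.842·√(0.07·0.93 + 0.04·0.96)]² / 0.03²

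- α = 0.05: (1.960·0.3224 + 0.842·0.3217)² / 0.0009 gives 906 per arm, 1812 in total.
- With continuity correction, n/4·[1 + √(1 + 4/(n·d))]²: 971 per arm, 1942 in total.
- α = 0.048: 917 per arm (1834 in total), or 983 (1966) with continuity correction.

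The corrected totals lie within 3% of 2000, so the stated size reproduces for an unstratified comparison. At 1000 per arm, power without the correction is 83.8% (α = 0.05) or 83.3% (α = 0.048).

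**2. Cost of omitting heparin type.** The documents give no DVT rate or patient share by heparin type, so ranges are assumed. The share of outcome variance between strata is w(1−w)(p₁−p₂)² / [p(1−p)]:

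- 60:40 split, 7% and 4%: 0.24·0.0009 / (0.058·0.942) = 0.40%.
- 50:50 split, 9% and 5%: 0.25·0.0016 / (0.07·0.93) = 0.61%.

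Of 2000 patients that is worth about 8 to 12.

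Simulation: 200,000 trials per setting, 1000 per arm, exact balance within strata, control rate averaging 7%, risk ratio 4/7 under the alternative, α = 0.048. It compares the crude chi-square with a Cochran-Mantel-Haenszel (CMH) test on two heparin strata.

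| Share in lower-risk stratum | Rate ratio between strata | Type I error, crude / CMH | Power, crude / CMH |
|---|---|---|---|
| 50% | 1 | 0.0483 / 0.0482 | 84.0% / 84.0% |
| 50% | 2 | 0.0469 / 0.0475 | 84.0% / 84.0% |
| 50% | 3 | 0.0453 / 0.0475 | 84.1% / 84.3% |
| 50% | 5 | 0.0445 / 0.0479 | 84.2% / 84.7% |
| 30% | 5 | 0.0456 / 0.0472 | 84.1% / 84.3% |

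The crude test is slightly conservative, and the largest loss is about 0.5 points of power.

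**3. Cost of two primary tests.** A center-stratified CMH test stood in for the mixed model: 16 centers of assumed unequal size, SD of log risk between centers 0 to 1.0 (assumed), 40,000 trials per setting.

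- The two conclusions differ in 0.005% to 2.5% of null trials and in 0.06% to 4.8% of trials under the design effect.
- If either test at 0.048 could claim success, type I error is about 0.045 to 0.047 with balance within center and about 0.051 to 0.059 without it. Two independent tests would give 1 − 0.952² = 0.094.

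**4. What the absolute interval would add.** As an illustration, suppose 5.5% is observed in both arms of 1000. The standard error is √(2·0.055·0.945/1000) = 0.0102, so the 95% interval is 0 ± 1.96·0.0102, about −2.0 to +2.0 points. That excludes a 3-point reduction, which is what a reader of a null result wants to know.

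**The case against.** The case for leaving the plan alone has force.

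- **Design and test match.** The sample size reproduces for an unstratified comparison, and the omission errs on the conservative side. This stands.
- **Heparin type is not ignored.** The plan's stated reason for stratifying is effect modification, and its interaction test addresses that. This stands, but an interaction test does not replace using the stratum in the main comparison.
- **The chi-square may be meant to decide.** The text compares groups by chi-square and uses the mixed model to estimate an adjusted risk ratio, so one test plus one adjusted estimate is a natural reading. The article never says so, and Table 1 gives both the same label.
- **The absolute interval can be recovered.** The risk ratio with its interval is reported in any case, and the counts would let a reader compute the risk difference. True, but conditioning the design-scale estimate on its own p value remains a stated rule and is easily removed.
- **The supplementary tables and full protocol are not shown.** They may say more. The points here rest on what the article itself states.

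Four stronger readings are tempting but not supported:

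- *The omission endangers power or validity.* Step 2 of the working shows that it does not.
- *Dozens of patients are wasted.* Such a figure needs the center variation as well. With an assumed center SD of 2 to 4 points around 5.5%, center accounts for 0.8% to 3.1% of outcome variance, but the mixed model already includes center.
- *Two primary tests double the false-positive rate.* They are highly correlated, and the worst assumed case is about 0.059.
- *The Cox model adjusts for post-randomization heparin use.* The sentence is framed around baseline imbalance, so the wording is loose rather than a stated on-treatment covariate.

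**Conclusion.** The point holds as a near-free improvement, not as a threat to the trial. The article names heparin type as a stratification factor, leaves it out of both analyses that it calls primary, does not say which of them decides at 0.048, and makes the absolute reduction conditional on significance.

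Ignoring the stratum costs at most about 0.5 points of power and lowers type I error to between about 0.044 and 0.048. The unnamed decisive test matters more: the two conclusions could differ in up to 4.8% of trials under the design effect in the least favorable assumed case. These sizes rest on assumed stratum rates and shares, center sizes and spread, and equal allocation. The analysis population is not in doubt, because Study population assigns the primary analysis to the intention-to-treat set.

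**What to change.** Before database lock:

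1. Name one decisive test at 0.048 in the intention-to-treat set that accounts for heparin stratum as randomized, for example a CMH test with two heparin strata. Crossing heparin with all 16 centers is not advised: up to 32 strata for about 70 + 40 = 110 expected events is 3 to 4 per stratum, and pooling small centers would need a rule that the plan lacks.
2. Add the heparin stratum to the mixed model, keep center as the random effect, and label that model and the crude chi-square supportive.
3. Report the risk difference with its confidence interval whatever the p value, next to the risk ratio.
4. State that heparin type, femoral line and dialysis in the adjusted Cox model are the values at randomization.
5. State which statistic served at the interim looks.

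The cost is plan wording and a few lines of code, with no new data and no change in sample size. One small downside should be disclosed. With 1620 of 2000 enrolled, both planned interim points (33% and 67%) have been passed in enrollment, so the final statistic may differ slightly from the interim one.

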**Methods/design:**

In this multicenter randomized trial, critically ill patients receiving pharmacologic thromboprophylaxis will be randomized to an IPC or a no IPC (control) group. The primary outcome is “incident” proximal lower-extremity deep vein thrombosis (DVT) within 28 days after randomization. Radiologists interpreting the lower-extremity ultrasonography will be blinded to intervention allocation, whereas the patients and treating team will be unblinded. The trial has 80% power to detect a 3% absolute risk reduction in the rate of proximal DVT from 7% to 4%.

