#### Mobility

Because mobility may influence the risk of DVT and because IPC may interfere with mobility, we will compare the highest level of mobility achieved each day and during the intervention duration between treatment groups. Mobility level will be assessed using a pre-defined continuous scale (0 nothing; 1 transfer from bed to chair without standing, 3 sitting in bed/exercises in bed, 4 sitting at edge of bed, 5 standing, 6 transfer from bed to chair with standing, 7 marching in place, 8 walking, and unknown) [11].

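### The secondary Cox/Kaplan-Meier analysis keeps patients at risk to day 28 after PE, ICU discharge or full mobility, when the plan no longer looks for or counts a primary DVT

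*Protocol article*

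**What the plan says.** All statements are in the Protocol article, which its Background presents as the trial's statistical analysis plan.

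- **Study design.** Ultrasonography is done at baseline and "twice weekly thereafter until the diagnosis of a lower-extremity DVT or PE, ICU discharge, death, full mobility or 28 days".
- **Primary outcome.** The event is "incident proximal lower-extremity DVT detected after the third calendar day of enrollment during the intervention period", and that period ends at "diagnosis of lower-extremity DVT, PE, ICU discharge, death, full mobility or 28 days".
- **Analysis of primary outcome.** The hazard at time *t* is defined given freedom from DVT up to *t*. The censoring rule follows: "Specifically, we will censor patients who are free of DVT by the end of the 28-day follow-up period, those who die before day 28". The only other group listed is dropouts and losses before day 28. Kaplan-Meier curves with a log-rank test and an adjusted Cox model accompany the unadjusted Cox model.
- **Analysis of primary outcome and Table 1.** Cox and Kaplan-Meier are secondary analyses. The primary analysis is a chi-square test with a risk ratio, plus a mixed model with center as random effect.
- **Mobility.** Mobility is compared between groups partly "because IPC may interfere with mobility".

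**The concern.** Six things end the period in which a primary event can be found: DVT, PE, ICU discharge, death, full mobility and day 28. The censoring list names only death, day 28 and loss to follow-up. A patient who leaves the ICU, becomes fully mobile or has a PE without a DVT is therefore carried to day 28 (or death) as DVT-free. After the exit, that freedom is assumed and not observed, which does not fit the plan's own definition of the hazard.

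Death is treated the other way, as ordinary censoring. The risk set thus behaves like a subdistribution risk set for discharge, mobility and PE, and like a cause-specific one for death. The resulting hazard ratio has no simple name.

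What is at stake is the use of the Cox model as a check on the risk ratio. The trial is open-label, and the plan itself raises the possibility that IPC affects mobility, one of the events that end surveillance. If surveilled time differs between arms, the crude risk ratio moves with it. A Cox model censored at the end of surveillance could help to show this. Under the rule as written, it largely repeats the crude result.

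**Working it through.** **1. The plan's own figures.** The article gives no figure for the time-to-event analysis. The nearest is 80% power for 7% versus 4% with 2000 patients. For two proportions, two-sided alpha 0.05 and 1:1 allocation (ratio assumed), the total is 1812 without and 1942 with continuity correction (1966 at alpha 0.048). So 2000 reproduces. The 7% and 4% also give ln(0.96)/ln(0.93) = 0.56 as a hazard ratio for illustration. Nothing below depends on the sample size.

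**2. Exits side by side.**

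| Exit without DVT | Surveillance and event window end? | Listed as censored? |
|---|---|---|
| Day 28 | yes | yes |
| Death | yes | yes |
| PE | yes | no |
| ICU discharge | yes | no |
| Full mobility | yes | no |

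**3. What the written rule estimates.** Let *h* be the DVT hazard while under surveillance and π(*t*) the share of the risk set still under surveillance. The hazard seen under the written rule is *h*·π(*t*), so the ratio between arms is (h₁/h₀)·(π₁(*t*)/π₀(*t*)). With equal stay the second factor is close to 1. With unequal stay it is not.

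**4. Illustration with constant hazards.** These inputs are assumptions, not in the document: *h* = 0.0065/day, chosen to give 7% detected; median time to end of surveillance 10 days, so *d* = ln 2/10 = 0.0693/day; death *m* = 0.008/day, so 1 − exp(−28 × 0.008) = 20% by day 28. Control arm at day 28:

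- Detected DVT: h/(h+d+m)·[1 − exp(−28(h+d+m))] = 0.0776 × 0.904 = 7.0%.
- Kaplan-Meier as written: h/(h+d)·[1 − exp(−28(h+d))] = 0.0857 × 0.880 = 7.5%.
- Kaplan-Meier censored at end of surveillance: 1 − exp(−28h) = 16.6%.
- All DVT to day 28, seen or unseen, with death competing: h/(h+m)·[1 − exp(−28(h+m))] = 0.448 × 0.334 = 15.0%.

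The written curve matches none of the other three. Its excess over 7.0% comes from censoring deaths and is modest.

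**5. Effect on the hazard ratio.** For a median surveilled stay of 12 days (IPC) versus 10 (control) and no IPC effect, π(*t*) = exp(−(h+d)t) / {1 − h/(h+d)·[1 − exp(−(h+d)t)]}. This gives 0.662/0.610 = 1.09 at day 7 and 0.433/0.367 = 1.18 at day 14. The fitted Cox model averages this drift. Simulation with 1,000,000 patients per arm:

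| Scenario | HR as written | HR censored at end of surveillance |
|---|---|---|
| No effect, IPC stay 9 v 10 days | 0.93 | 0.99 |
| No effect, 11 v 10 | 1.06 | 1.00 |
| No effect, 12 v 10 | 1.11 | 1.00 |
| True HR 0.56, equal stay | 0.561 | 0.555 |
| True HR 0.56, 12 v 10 | 0.626 | 0.556 |

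In the 12 v 10 row with no effect, the crude risk ratio is 1.109, almost the same as the written HR.

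**6. Sensitivity to the stay distribution.** Other assumptions: log-normal stay, median 8 days, log-SD 0.8; death 0.008/day; DVT 0.0105/day from day 3. With no effect and a 20% longer IPC stay, repeated runs give 1.20 to 1.22 as written and 0.99 to 1.00 when censored at end of surveillance. With a true HR of 0.57 and the same stay difference, 0.70 against 0.57. With equal stay, 0.583 against 0.575 in one run.

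**7. Limits of the alternative.** When a latent severity factor is assumed to raise both stay and DVT hazard, with no true effect and a 20% longer IPC stay, censoring at end of surveillance gives 0.92 to 0.96, not 1.00. Gray's test does not help either: in the log-normal scenario with no effect, the subdistribution HR is 1.20, the same as the written rule.

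**The case against.** **This is a secondary analysis.** That stands. The chi-square test, the risk ratio and the mixed model do not use the censoring rule. A reader might infer that the primary result is compromised; it is not, at least by this rule. The crude risk ratio does depend on length of surveillance, but that comes from the definition of the event window and is a separate matter.

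**The size of the bias rests on an effect the plan does not assert.** This stands as well. The plan says IPC may interfere with mobility, as a reason to compare mobility. It does not say that IPC lengthens stay, still less by 20%. The excess also roughly halves or doubles with the assumed stay distribution.

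**Loss to follow-up could cover discharge.** This is hard to sustain. Discharge and full mobility are planned ends of surveillance, and mortality is assessed to 90 days, so these patients are not lost. The list is introduced as a specific one, so this is not a detail left to another document.

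**The plan already has safeguards.** It compares ultrasound counts and timing, mobility and ICU stay between arms; it has a composite with 28-day mortality and a sensitivity analysis in patients alive and in the ICU for at least 14 days. The comparisons would reveal unequal surveillance. None of these changes the Cox or Kaplan-Meier rule.

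**A second outcome window.** A reader might infer one from the Abstract's "proximal lower-extremity deep vein thrombosis (DVT) within 28 days after randomization". It is better read as shorthand for the 28-day cap in the Primary outcome section, and no point is made of it.

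**Conclusion.** The mismatch holds on the text alone: three planned ends of surveillance are missing from an explicit censoring list. It is a moderate point, because it touches only a secondary analysis.

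The hazard ratio is hardly affected if surveilled stay is equal between arms. If stay differs, it largely repeats the surveillance bias of the crude risk ratio: about 1.1 to 1.2 with no true effect and a 20% longer IPC stay, and in the other direction for a shorter stay. These sizes rest on assumed stay, mortality and DVT rates. The curves are off in either case, modestly (7.5% against 7.0% detected in the illustration).

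It would be tempting to say that correct censoring removes the bias. It does so only if the end of surveillance is non-informative given covariates, which the document cannot establish.

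**What to change.** 1. In the unadjusted and adjusted Cox models, censor at the end of the intervention period exactly as the Primary outcome section defines it: PE, ICU discharge, death, full mobility or day 28. Report the result as a cause-specific hazard ratio under surveillance.
2. State the assumption that end of surveillance is non-informative given covariates. This is the main downside of the change. The adjusted Cox model gives some support, but its listed covariates include no severity score, so the support is partial.
3. For absolute risk, replace the Kaplan-Meier curves by cumulative incidence curves with death, PE and end of surveillance as competing exits, and label them as detected incidence.
4. Use the cause-specific log-rank or Cox test for the hazard comparison. Do not present Gray's test as a correction for unequal surveillance, because it keeps discharged patients in the risk set.

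The cost is wording and standard code, before database lock. The exit dates define the primary outcome and should already be recorded. The primary analysis and the sample size do not change.
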